## Abstract

**Introduction:**

Anginal symptoms and signs of ischemia have been reported in some patients with cardiac transthyretin amyloidosis (ATTR) without obstructive epicardial coronary artery disease (CAD). Few studies found that coronary microvascular dysfunction was highly prevalent in subjects with cardiac amyloidosis, even in the absence of epicardial CAD. The purpose of this study is to confirm the coronary microvascular dysfunction, and to go further with evaluation of the effect of Tafamidis on microvascular dysfunction after 24 months of treatment.

**Methods and analysis:**

This study is a multicentric, prospective, observational cohort study. Adult patients with confirmed ATTR cardiomyopathy seen in the nuclear medicine departments of three large referral centers and treated with Tafamidis will be included. At baseline, patients will have a clinical and echocardiography evaluation. They will undergo a dynamic rest/stress cardiac scintigraphy with flow and reserve measurements before and 24 months after Tafamidis introduction. The primary outcome of this study will be the variation of stress and rest myocardial blood flow and flow reserve between baseline and 24 months after treatment. The effect of Tafamidis will be assessed by an intention to treat analysis.

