New therapeutic options are arising in cardiac ATTR. In a multicentric, international, double-blind, placebo-controlled, phase 3 trial, including 441 patients with ATTR cardiomyopathy, Maurer et al. showed that Tafamidis (80 mg and 20 mg) was associated with reductions in all-cause mortality (78 of 264 [29.5%] vs. 76 of 177 [42.9%]; hazard ratio, 0.70; 95% confidence interval [CI], 0.51–0.96) and cardiovascular-related hospitalizations after 18 months [relative risk ratio of 0.68 (0.48 per year vs. 0.70 per year; 95% CI, 0.56–0.81)], and reduced the decline in functional capacity and quality of life after 6 months as compared with placebo in patients with transthyretin amyloid cardiomyopathy (15). Tafamidis has now been approved for patients with ATTR cardiomyopathy and is recommended class I in the latest European guidelines on heart failure (16).

In APPOLO trial (international, randomized, double-blind, placebo-controlled phase 3 trial with hereditary ATTR amyloidosis), Patisaran, by stopping the synthesis of TTR through gene silencing, decreased mean left ventricular wall thickness, global longitudinal strain, N-terminal prohormone of brain natriuretic peptide, and adverse cardiac outcomes compared with placebo at month 18 (17). Authors used Patisaran 0.3 mg/kg IV once every 3 weeks in 225 ATTR-FAP patients. Others pharmacological trials explored Inotersen treatment (gene silencer too), but they focused on neurological disease: NEURO-TTR phase 3 trial (18).

About others tetramer stabilizers, no beneficial cardiac effect has been shown in Diflunisal treatment, and a randomized double-blind, placebo-controlled Phase 2 trial has been initiated, as mentioned in a recent mini review (19).

To our knowledge, no study focused on the effect of cardiac amyloidosis treatment on microvascular dysfunction.

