## Methods and analysis

### Study protocol

This is a multicentric, prospective, observational cohort study involving three French academic hospitals (University Hospital of Angers, University Hospital of Tours and Regional Hospital of Orleans). Study patients will enter the cohort after they have been diagnosed with cardiac ATTR, including ^99m^Tc-PYP scintigraphy (grade 2 or 3) (20–22), according to the diagnostic algorithm for cardiac ATTR proposed by Gillmore et al., after they meet inclusion/exclusion criteria (Table 1).

**TABLE 1 T1:** Inclusion and exclusion criteria.

Inclusion criteria	Exclusion criteria
● Patients aged from 18 to 90 years	● Other heart failure cause (not ATTR)
● Understanding and speaking French ● With TTR amyloid cardiomyopathy (ATTRxt or ATTRm) confirmed by the association of: ⚬ clinical heart failure (NYHA I-III) ⚬ with echocardiogram and/or magnetic resonance imaging suggesting/indicating cardiac amyloidosis, ⚬ grade 2 or 3 99mTc PYP or bone scintigraphy, ⚬ and negative biological findings (i.e., serum immunofixation, urine immunofixation, serum free light chain assay), or, if one of those criteria is not met, amyloid deposits on biopsy specimens (from cardiac and non-cardiac sites), ● Intention to treat (Tafamadis)	● New York Heart Association (NYHA) class IV heart failure. ● Light-chain amyloidosis ● Liver or heart transplantation history ● Glomerular filtration rate below 25 mL per minute per 1.73 m^2^ of bodysurface area (Cockroft) ● High liver transaminase levels (two times the upper limit of the normal range) ● Severe malnutrition defined by a modified body-mass index (mBMI: serum albumin level in grams per litter multiplied by the conventional BMI) of less than 600; ● Concurrent treatment with non-steroidal anti-inflammatory drugs, tauroursodeoxycholate, doxycycline, calcium-channel blockers, digitalis, or ticagrelor ● Previous treatment with tafamidis or patisaran ● Previous CAD, severe epicardial stenosis with revascularization or ticagrelor treatment, coronary artery bypass grafting, myocardial infarction ● Contra-indications to pharmacological stress testing MPI: severe hypotension (<90 mmHg of Systolic arterial pressure), atrioventricular block 2nd or 3rd grade, carotid stenosis (unilateral > 70%, bilateral > 50%) ● Pregnancy ● Breastfeeding ● Protected adults

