**FIGURE 2 F2:**
[figure not shown]
Dynamic scintigraphy protocol.

Epicardial obstructive CAD will be ruled out in subjects with pathological initial imaging (coronary angiography or cardiac CT depending on the cardiologist choice). Patients with epicardial stenosis will be analyzed apart, especially if revascularization or ticagrelor treatment is performed.

Visits are mainly already included in the cardiologic follow-up of the Tafamidis treatment at 6, 12, 18, and 24 months (with cardiac echography at 12 and 24 months). Clinical data and echocardiography findings will be resumed. Clinical data will include blood pressure, NYHA class, Kansas City Cardiomyopathy Questionnaire-Overall Summary (KCCQ-OS), 6-min walking test, electrocardiogram, any treatment interruption, or hospitalization. Cardiac echography will include at least: left ventricles volumes measurement, ejection fraction, wall thickness, strain results.

Last evaluation will be CZT SPECT MPI after 24 months of treatment, in the same conditions as baseline.

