### Trial outcomes

The primary outcome is the variation of stress and rest MBF and MFR assessed by dynamic SPECT, between baseline and 24 months after Tafamidis treatment.

The secondary outcomes are:

•Results from baseline dynamic SPECT, confirming the stress and rest MBF and MFR reduction in cardiac ATTR patients,•Results from echo/MRI.

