### Statistical analysis plan

Interim analysis is planned after all inclusions for MBF and MFR baseline evaluation. Final analysis is planned after completion of study. A subgroup with patients suffering from CAD, assessed by invasive coronary angiography or cardiac-CT after baseline SPECT will be analyzed apart.

All MBF and MFR values will be described as mean ± SD. Normal distribution of the value will be evaluated. Comparisons between continuous variables will be performed using two-tailed paired *t*-test. Non-parametric variables will be listed as medians and compared using the Mann–Whitney *U* test. Discrete variables will be described as proportions and compared with the chi-square test. Correlations will be performed using Pearson R or non-parametric methods (Spearman rho) as indicated. Multivariable linear regression analyses will be performed to study the independent contributions of various parameters on stress MBF and MFR.

The total number of patients expected in this “proof of concept” study is 50 patients. In the context of a pilot study, the workforce calculation is not applicable, as frequently in the case of exploratory studies on innovative technologies (24). This number of patients is also compatible with the recruitment capacities of the three investigative centers.

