With this study, we aim to demonstrate an impact of Tafamidis on microvascular dysfunction. Regarding our secondary endpoint, various perspectives can be seen. Firstly, the absence or low proportion of microcirculatory dysfunction in patients with cardiac amyloidosis. However, the sample size remains small, and the evaluation may be too early compared with the diagnosis (although often late); this is therefore a possible limitation of our study, which may explain the failure to find this microcirculatory dysfunction. The second option is a high proportion of microcirculatory dysfunction in patients with cardiac amyloidosis. Our hypothesis would then be confirmed and will therefore be in line with the study of Dorbala et al. performed in PET (4). Other studies also found microcirculatory dysfunction in these patients, as well as in other infiltrative heart diseases such as sarcoidosis (30), which reinforces the probability of this option.

Regarding the variation in MFR values after treatment, the first possibility is a significant decrease of MFR. In this case, the primary hypothesis of an improvement in microcirculatory dysfunction after treatment with Tafamidis would then not be verified. Thus, the lack of effect of Tafamidis on microcirculatory damage would be considered, and the benefits on overall survival, quality of life and cardiovascular events mentioned in the previous studies would probably be due to another pathophysiological process. However, an aggravating factor of Tafamidis on microcirculatory function could not be raised in our study in the absence of a “control” population (untreated or benefiting from another treatment), so another study with this objective could be envisaged, in order to distinguish the natural evolution of the pathology from a treatment effect.

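### The abstract calls the analysis intention to treat, but the paired test described can use only patients with both scans, so the estimate is a change among those alive and rescanned at 24 months

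*Protocol article*

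**What the plan says.** - Abstract, Methods and analysis: "The effect of Tafamidis will be assessed by an intention to treat analysis". The body of the article does not repeat or define this. Table 1 uses the same phrase only as an inclusion criterion, meaning that Tafamidis is planned.
- Study protocol: "This is a multicentric, prospective, observational cohort study involving three French academic hospitals". The Discussion concedes that a worsening could not be attributed to the drug "in the absence of a “control” population (untreated or benefiting from another treatment").
- Under Trial outcomes, the endpoint is given as: "The primary outcome is the variation of stress and rest MBF and MFR assessed by dynamic SPECT, between baseline and 24 months after Tafamidis treatment".
- Interventions and participant timeline, text after Figure 2: "Last evaluation will be CZT SPECT MPI after 24 months of treatment". No perfusion scan is planned between baseline and that one.
- Statistical analysis plan: "Comparisons between continuous variables will be performed using two-tailed paired" t-test. The same section takes out some included patients: "A subgroup with patients suffering from CAD", identified by angiography or cardiac CT after the baseline scan, is to be analysed separately.
- Current knowledge: the cited phase 3 trial had 78 deaths among 264 patients on Tafamidis (29.5%) and 76 among 177 on placebo (42.9%).

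**The concern.** An intention-to-treat label tells the reader that everyone who started treatment counts in the result, whatever happened afterwards. A paired test on one follow-up scan cannot deliver that, because a patient without the second scan has no difference to analyse. Moving CAD cases to a separate analysis narrows the set further, on a finding made after inclusion.

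In this disease the loss is unlikely to be small or random: patients may die or become too unwell to be scanned. If those patients would also have had the worse flow changes, the mean change in the rest looks better than the mean change in all who were treated. The Discussion says that a significant rise in myocardial flow reserve (MFR) would confirm a possible mechanism of clinical benefit. With no control group, nothing in the design would expose selective loss, and the label would suggest that it had been dealt with.

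**Working it through.** **1. The label against the analysis.** The article fixes one label (intention to treat), one test (paired t-test) and one follow-up scan (24 months). A paired difference needs both values, so the analysed set is the patients with both scans, less any CAD cases analysed apart. The non-parametric alternative named in the same section also needs an observed 24-month value. Intention to treat would hold only if nobody died or missed the scan and the CAD cases stayed in.

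**2. The cited mortality.** 78/264 = 29.5% and 76/177 = 42.9%. Both printed percentages reproduce.

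**3. Expected number of pairs.** The article does not say at what month the 29.5% was reached. Take that month as L and assume a constant hazard:

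pairs = 50 × (1 − 0.2955)^(24/L)

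| L (months, assumed) | 24-month mortality | Deaths of 50 | Pairs |
|---|---|---|---|
| 18 | 37.3% | 18.7 | 31.3 |
| 24 | 29.5% | 14.8 | 35.2 |
| 30 | 24.4% | 12.2 | 37.8 |
| 36 | 20.8% | 10.4 | 39.6 |

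This gives about 31 to 40 pairs, before any loss other than death. The paired change detectable with 80% power (two-sided 5%, assumed because no level is stated) rises from 0.40 SD with 50 pairs to 0.45 SD with 40 and 0.49 SD with 35.

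**4. Possible bias.** Suppose the true mean change is zero. Let d be the share without a second scan and rho the correlation between a patient's flow change and a normally distributed tendency to be rescanned. In SDs of change,

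bias = rho × φ(z_d) / (1 − d)

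where z_d is the normal quantile at d and φ the normal density. At d = 0.295, z_d = −0.539 and φ = 0.345, so φ/(1 − d) = 0.345/0.705 = 0.489.

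- rho = 0.3: 0.3 × 0.489 = +0.147 SD
- rho = 0.5: 0.5 × 0.489 = +0.245 SD
- rho = 0: no bias
- rho = −0.3: −0.147 SD

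At d = 0.15, rho of 0.3 and 0.5 give +0.082 and +0.137 SD. In simulation with 50 enrolled and 29.5% loss, the two-sided 5% test declares improvement in about 14% (rho 0.3) and 32% (rho 0.5) of trials, against 2.5% with no selection.

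**5. Mechanisms that do not favour improvement.** At 24.5% loss, if loss depends only on true baseline flow and change is unrelated to it, the simulated bias is about zero. If loss follows a low measured baseline value, regression to the mean gives about −0.13 SD (reliability 0.8) to −0.19 SD (reliability 0.6), away from improvement.

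**The case against.** - **The rule may stand elsewhere.** Analysis sets and missing-scan handling often stand only in the full protocol or SAP, and the article never says completers only. That is right, and silence on missing data is not the finding. The finding is that the article itself fixes a label and a test that do not agree.
- **In a single-arm cohort the phrase may only mean that patients who interrupt Tafamidis are kept.** That is a reasonable reading, but a paired test respects it only for those who are rescanned.
- **The CAD rule is prespecified and reasoned.** This stands. Previous CAD is an exclusion criterion, disease prompted by the baseline scan was largely present at entry, and the Discussion explains the separation. It is not an exclusion driven by outcome. It still means that not everyone included is in the main analysis, and the article should say so.
- **The size rests on borrowed and assumed figures.** This also stands. The mortality is from another trial, pooled over two doses, with no clear horizon, and the correlations are assumed.

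A reader might infer that the result is biased towards improvement as a matter of fact. The document does not support that: nothing in it links flow change to death or to a missed scan, and step 5 of the working shows nil or reversed bias under other mechanisms.

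A reader might also infer two different timings for the last scan, because the abstract counts from the introduction of Tafamidis and the timeline section from treatment received. These are near-paraphrases. The article records interruptions and nowhere delays the scan or drops patients who interrupt, so no conflict is shown.

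**Conclusion.** The intention-to-treat statement does not match the analysis that the article describes. The result will be a mean change among patients alive and rescanned at 24 months, with the place of the CAD cases in the primary set left unclear. This follows from the text alone.

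The size is conditional. If the cited mortality carries over, between a fifth and somewhat more than a third of the 50 patients would have no pair. That is too many to leave out under a label that implies they are counted. Bias towards improvement is plausible if patients who deteriorate are less often rescanned, but its direction and size remain unknown. The study is a 50-patient proof of concept that admits it has no control group. That limits what any result can show, but it does not make the label correct.

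**What to change.** 1. Replace the intention-to-treat label with a plain description: *change in patients with both scans, regardless of Tafamidis interruption*.
2. State whether patients found to have CAD after the baseline scan belong to the primary set.
3. Report how many 24-month scans are missing and why (death, cardiac worsening, other), and tabulate baseline MFR for patients with and without that scan.
4. Add a sensitivity analysis over all treated patients in which death, or inability to be rescanned because of cardiac worsening, ranks as the worst outcome. This can be a worst-rank signed-rank test, or the proportion alive with improved MFR out of all treated.

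A likelihood-based mixed model should not be offered as the remedy for this bias. It assumes data are missing at random, whereas the worry is loss tied to the unseen change itself. In the simulation at 29.5% loss, with baseline unrelated to change, it returned the same bias as the paired analysis (+0.147 SD at rho 0.3). It would also project a 24-month flow for patients who have died, which does not fit an estimate among those alive.

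The cost is a change of wording and a little analysis work, with no new patients or scans. The downside is that the all-treated result may be less favourable than the paired one.

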**Ethics and dissemination:**

The study has received the following approvals: Orleans Hospital Research Committee (CHRO-2021-05) and Sud-Mediterranée IV Regional Ethics Committee (21 06 02). Results will be made available to physicians, the funders, and other researchers.

**Clinical trial registration:**

[https://clinicaltrials.gov/ct2/show/NCT05103943], identifier [NCT05103943].

## Introduction

### Context

Systemic amyloidosis represents rare conditions in which the gradual extracellular accumulation of insoluble fibrillar proteins disrupts the structure of the affected tissues and causes organ impairment. Transthyretin amyloidosis (ATTR) commonly affects the heart. The amyloid deposits cause an increase in ventricular wall thickness and result in restrictive cardiomyopathy presenting primarily as biventricular congestive heart failure. Ischemia signs and anginal symptoms have been described in some individuals with cardiac amyloidosis and without obstructive epicardial coronary disease (CAD) (1–3).

### Current knowledge

Dorbala et al. found that coronary microvascular dysfunction was highly prevalent in patients with cardiac amyloidosis, even in the absence of epicardial CAD, and might explain their anginal symptoms. They found lower stress and rest myocardial blood flow (MBF) and lower myocardial flow reserve (MFR) in their cardiac PET study (using ^13^N), including 21 patients with definite cardiac amyloidosis without epicardial CAD (4). Moreover, reduction of MFR during cardiac amyloidosis has also been described using myocardial contrast echocardiography (5).

The use of cadmium zinc telluride (CZT) detectors in SPECT technology allows acquisition in a non-rotating mode and therefore acquisition of time–activity curves, and improves sensitivity and temporal resolution (6). Thus, absolute MBF and MFR estimation by SPECT becomes possible as shown in experimental animal models (7) and also in clinical studies with comparison to PET (8–11), with a good correlation between those two techniques. SPECT myocardial perfusion imaging (MPI) showed, in a recent sub-study of the PACIFIC trial, a low per-vessel sensitivity [42%, confidence interval (CI): 34–50%] in comparison to PET (81% CI: 72–87%) and a low per-patient sensitivity for detection of CAD: 61% (CI: 48–72%) vs. 90% (CI: 80–96%), respectively, for SPECT and PET. However, specificity was 93% (CI: 85–97%) and 87% (CI: 78–93%) for SPECT and PET. Using the entire cohort of patients and vessels, and regarding the diagnostic performances of imaging modalities for significant CAD with an intention-to-diagnose, per-patient area under the receiver operating characteristic curve and diagnostic accuracy were outperformed by PET (0.90 and 86%; *p* = 0.005 and *p* < 0.001, respectively) in comparison to SPECT (0.74 and 76%, *p* = 0.087 and *p* = 0.266, respectively) (12). Moreover, PET imaging enables higher spatial resolution and enhanced image quality (13). Thus, PET has become a reference, also thanks to added parameters in PET in comparison with SPECT: dynamic PET and systematic CT that enables calcium scoring. MBF and MFR incrementally improve diagnostic and prognostic accuracy over MPI alone. 82-Rubidium or 13N-Ammonia PET imaging with pharmacological stress MPI, MBF, and MFR can be acquired simultaneously without incremental cost, radiation exposure, or significant processing time (14). Nuclear cardiology clinics with PET access have incorporated MBF quantification into clinical routine, but this is not the case for conventional SPECT MPI. However, especially in Europe, cardiac PET remains of difficult access in comparison to SPECT and now CZT SPECT.

New therapeutic options are arising in cardiac ATTR. In a multicentric, international, double-blind, placebo-controlled, phase 3 trial, including 441 patients with ATTR cardiomyopathy, Maurer et al. showed that Tafamidis (80 mg and 20 mg) was associated with reductions in all-cause mortality (78 of 264 [29.5%] vs. 76 of 177 [42.9%]; hazard ratio, 0.70; 95% confidence interval [CI], 0.51–0.96) and cardiovascular-related hospitalizations after 18 months [relative risk ratio of 0.68 (0.48 per year vs. 0.70 per year; 95% CI, 0.56–0.81)], and reduced the decline in functional capacity and quality of life after 6 months as compared with placebo in patients with transthyretin amyloid cardiomyopathy (15). Tafamidis has now been approved for patients with ATTR cardiomyopathy and is recommended class I in the latest European guidelines on heart failure (16).

In APPOLO trial (international, randomized, double-blind, placebo-controlled phase 3 trial with hereditary ATTR amyloidosis), Patisaran, by stopping the synthesis of TTR through gene silencing, decreased mean left ventricular wall thickness, global longitudinal strain, N-terminal prohormone of brain natriuretic peptide, and adverse cardiac outcomes compared with placebo at month 18 (17). Authors used Patisaran 0.3 mg/kg IV once every 3 weeks in 225 ATTR-FAP patients. Others pharmacological trials explored Inotersen treatment (gene silencer too), but they focused on neurological disease: NEURO-TTR phase 3 trial (18).

About others tetramer stabilizers, no beneficial cardiac effect has been shown in Diflunisal treatment, and a randomized double-blind, placebo-controlled Phase 2 trial has been initiated, as mentioned in a recent mini review (19).

To our knowledge, no study focused on the effect of cardiac amyloidosis treatment on microvascular dysfunction.

